#### Multivariate Regression Analyses

In addition, we will conduct hypothesis-generating multivariate regression analyses of the outcomes. For those models, the independent variables will consist of the kinematic/kinetic and neurophysiological scores, and the dependent variable will be the ARAT, Fugl-Meyer, or BBT score. We will also conduct separate regression models for each of the dependent variables. While modeling potential intrinsic correlation between VR measurements taken on the same person via multivariate models, potential collinearity among covariates will be investigated and appropriate regularization will be implemented accordingly. Collinearity analysis may also inform us whether some VR games might be redundant, and aid in future development of VR therapies. Finally, suitable contrasts for hypotheses related to comparing VR performance score among the first and last 2 days of therapy, and the two retention tests will be considered.

#### Management of Statistical Assumptions

For all analyses, model-related assumptions will be examined. For example, in case that normality assumption required by linear mixed effects model cannot be met, appropriate transformation to center the dependent variables will be first sought. If no appropriate transformation is applicable, non-parametric mixed models will be applied. Collinearity between covariates will be examined with variance inflation factor (multilevel variance inflation factor to the case of mixed effects models). Appropriate selection from collinear covariates will be based on knowledge or literature. Statistical methods like principal component analysis will be used to extract factors from collinear covariates when needed.

#### Management of Missing Data and Dropouts

Besides listwise exclusion, which assumes missing data completely at random, multiple imputation methods will be used as a sensitivity analysis to examine the effect of different assumptions about missing data.

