## Abstract

**Introduction:** Innovative motor therapies have attempted to reduce upper extremity impairment after stroke but have not made substantial improvement as over 50% of people post-stroke continue to have sensorimotor deficits affecting their self-care and participation in daily activities. Intervention studies have focused on the role of increased dosing, however recent studies have indicated that timing of rehabilitation interventions may be as important as dosing and importantly, that dosing and timing interact in mediating effectiveness. This study is designed to empirically test dosing and timing.

**Methods and Analysis:** In this single-blinded, interventional study, subjects will be stratified on two dimensions, impairment level (Fugl-Meyer Upper Extremity Assessment (FM) and presence or absence of Motor Evoked Potentials (MEPs) as follows; (1) Severe, FM score 10–19, MEP+, (2) Severe, FM score 10–19, MEP–, (3) Moderate, FM score 20–49, MEP+, (4) Moderate, FM score 20–49, MEP–. Subjects not eligible for TMS will be assigned to either group 2 (if severe) or group 3 (if moderate). Stratified block randomization will then be used to achieve a balanced assignment. Early Robotic/VR Therapy (EVR) experimental group will receive in-patient usual care therapy plus an extra 10 h of intensive upper extremity therapy focusing on the hand using robotically facilitated rehabilitation interventions presented in virtual environments and initiated 5–30 days post-stroke. Delayed Robotic/VR Therapy (DVR) experimental group will receive the same intervention but initiated 30–60 days post-stroke. Dose-matched usual care group (DMUC) will receive an extra 10 h of usual care initiated 5–30 days post-stroke. Usual Care Group (UC) will receive the usual amount of physical/occupational therapy.

**Outcomes:** There are clinical, neurophysiological, and kinematic/kinetic measures, plus measures of daily arm use and quality of life. Primary outcome is the Action Research Arm Test (ARAT) measured at 4 months post-stroke.

**Discussion:** Outcome measures will be assessed to determine whether there is an early time period in which rehabilitation will be most effective, and whether there is a difference in the recapture of premorbid patterns of movement vs. the development of an efficient, but compensatory movement strategy.

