### Sample Size

For Aim 1, the planned primary analysis method is a mixed effect model. The primary outcome measure is the change in ARAT score from baseline evaluated at 4 months post-stroke. The estimated effect size for the interaction term is 0.42 (Cohen's f), and the estimated within-subject correlation is 0.7. For testing the hypothesis of Treatment Group (EVR, DVR, UC, DMUC) ^*^Test Time (Baseline, 4 M post-stroke, 6 M post-stroke) effect, and assuming compound symmetry correlation for within-subject measurements, for significance level 0.05, a total of 84 patients (21 for each group) are needed to detect the overall Treatment Group ^*^ Test Time interaction effect. But for the main planned contrasts, Treatment Group (EVR, DVR) ^*^ Test Time (Baseline, 4 M post-stroke) and Treatment Group (UC, DMUC) ^*^ Test Time (Baseline, 4 M post-stroke), a total of 96 patients (24 for each group) are required to detect the effect size of 0.42 between EVR and DVR or between UC and DMUC over time. Since detecting these contrasts is the main goal of the study, at least 96 subjects, 24 subjects per group, are required. After taking into account subject attrition, our total sample size will be equal to 120. We plan to run an interim analysis and update the sample size when we have recruited 50% of subjects.

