We will use the robust mixed effect model approach to analyze the data. We demonstrated in the past that this analytic approach is robust to detect treatment effects, even with relatively small groups of patients in whom within-group variance occurs with respect to stroke characteristics (56). Test Time (Pre, Post, 1-month post-treatment, 4 months post-stroke, 6 months post-stroke) and Treatment Group (EVR, DVR, DMUC, UC) will be treated as fixed effects in the mixed models. The interaction term between Test Time and Treatment Group will be included. Baseline measurements will be added as a covariate into mixed models for outcome variables. Random intercept will be used to model subject-level variation. Covariance pattern and model selection will be implemented with likelihood-based tests. Contrasts to compare group means will be applied to obtain comparisons between time, and between treatments, with multiplicity adjustment considered. We have an a priori interest in specific Test Time by Treatment Group interaction effects for the EVR-DVR, for the DMUC-UC, and for the EVR-DMUC comparisons. The particular differences we are interested in are Pre vs. Post and Pre vs. second (4 months post stroke) retention assessments. In the case of balanced data and equal variances, we will use the Tukey procedure to test for significant interaction effects, otherwise, Bonferroni correction will be used. In our design, the timing comparison is the difference between EVR and DVR. The dosage comparison is the difference between UC (usual care) and the DMUC (usual care plus 10 additional hours). In addition, we will be able to compare the type of training effect, VR vs. dose-matched usual care (EVR vs. DMUC), where both types of training are delivered in the same time period.

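### Listwise exclusion, stated to assume MCAR, is the main missing-data approach; at patient level it would drop patients who have the 4-month ARAT and give up the mixed model's validity under MAR

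*Protocol article*

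**What the plan says.** The section Management of Missing Data and Dropouts is a single sentence: "Besides listwise exclusion, which assumes missing data completely at random, multiple imputation methods will be used as a sensitivity analysis". It names two approaches, ties the first to MCAR and calls the second a sensitivity analysis. It does not say whether the unit removed is a patient or a single visit record.

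The Statistical Analysis section says "We will use the robust mixed effect model approach to analyze the data". The time factor has five levels, "Test Time (Pre, Post, 1-month post-treatment, 4 months post-stroke, 6 months post-stroke". On the subject effect it says "Random intercept will be used to model subject-level variation", and on baseline "Baseline measurements will be added as a covariate into mixed models for outcome variables".

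The Abstract fixes the endpoint: "Primary outcome is the Action Research Arm Test (ARAT) measured at 4 months post-stroke".

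The Sample Size section requires 24 per group for the main contrasts and then states "After taking into account subject attrition, our total sample size will be equal to 120". No section says that partly observed patients stay in the primary model or that the model relies on MAR.

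**The concern.** The missing-data rule and the model pull in different directions. A likelihood mixed model with a subject random intercept uses every visit a patient attended and is valid when missingness depends only on observed data. Listwise exclusion at patient level discards that. A patient seen at Pre, Post, 1 month and 4 months who misses only the 6-month visit would be lost from the 4-month comparison, although the primary endpoint was measured.

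Two things are at stake. The first is precision: the contrast would use fewer patients than have the primary outcome, and possibly fewer than the 24 per group the plan requires. The second is selection: the analysed patients would be those with complete follow-up, and the comparison is sound only if completeness is unrelated to outcome. MCAR is doubtful here because visit burden differs between the two arms of the primary contrast. Under Measures, DVR has an additional assessment, and under Interventions its training starts 30–60 days post-stroke, whereas EVR trains alongside inpatient care.

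**Working it through.** **Inputs from the article.** Cohen's f = 0.42 and significance level 0.05 (Sample Size); 24 per group for the main contrasts, 120 in total (Sample Size); 30 per group (Randomization and Recruitment); five test times, so four after baseline (Statistical Analysis). Power is not stated; 80% is assumed.

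**Step 1: reproduce the plan's figures.** Use the noncentral F distribution with λ = f² × N.
- Contrast, 2 groups × 2 times, 24 per group: λ = 0.42² × 48 = 8.47, df 1 and 46, power 0.813. With 23 per group power is 0.796, so 24 is the smallest size reaching 0.80.
- Overall interaction, 4 groups × 3 times, 21 per group: λ = 0.42² × 84 = 14.8, df 6 and 160, power 0.821. With 20 per group it is 0.797.
- Attrition: 96 / 0.80 = 120, so the implied rate is 20%. The article does not state it.

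The stated sample sizes reproduce and are not in question.

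**Step 2: patients kept under each rule.** The article gives no missingness rate by visit. Assume a rate q at each of the four post-baseline visits, independent between visits, with baseline present for everyone.
- With a 4-month ARAT, per arm: 30 × (1 − q)
- Kept by listwise exclusion, per arm: 30 × (1 − q)⁴

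Power uses the formula of Step 1 with λ = f² × 2n and df 1 and 2n − 2, where n is the number per arm.

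| q per visit | With 4-month ARAT, per arm | Kept listwise, per arm | Power, all with 4-month ARAT | Power, listwise |
|---|---|---|---|---|
| 3% | 29.1 | 26.6 | 0.88 | 0.85 |
| 5% | 28.5 | 24.4 | 0.88 | 0.82 |
| 8% | 27.6 | 21.5 | 0.87 | 0.77 |
| 10% | 27.0 | 19.7 | 0.86 | 0.73 |
| 20% | 24.0 | 12.3 | 0.81 | 0.51 |

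At 5%, 120 × (0.950 − 0.815) ≈ 16 randomised patients would be dropped although their 4-month ARAT is available; at 10%, 120 × (0.900 − 0.656) ≈ 29.

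**Step 3: the threshold.** Listwise exclusion keeps 24 of 30 when (1 − q)⁴ = 0.80, that is q = 1 − 0.80^(1/4) = 5.4%.

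**Step 4: another missingness pattern.** If patients drop out and do not return, with an assumed 20% lost by month 4 and 30% by month 6, then 24 per arm have the 4-month ARAT and listwise exclusion keeps 21. Power is 0.81 against 0.76.

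**Step 5: direction of bias.** In an illustrative simulation (30 per arm, SD 1, within-subject correlation 0.7, no missing 4-month values), about 26% missed the 6-month visit, depending on the 4-month score in opposite directions by arm. Listwise exclusion biased the 4-month difference by about 0.59 SD; the likelihood model on all available data was off by about 0.01 SD. This pattern was made deliberately strong. It shows that bias can arise, not how large it would be in this trial.

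**The case against.** The strongest reply is that the sentence is brief, does not name the ARAT or the primary analysis, and does not define what is deleted. It follows sections on regressions and on assumptions for all analyses, where complete-case deletion is a common default. If only records with a missing score are dropped, the mixed model keeps partly observed patients and little is lost. The ambiguity is real. But that reading does not fit the article's own MCAR remark, because a likelihood mixed model on the remaining records needs only MAR. On either reading the sentence needs correcting.

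A second reply is that multiple imputation is already planned to examine other assumptions. It is, and it could expose a problem, but as a sensitivity analysis it would not change the primary estimate.

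A reader might also infer more than the text supports:
- That DVR patients must complete six visits to be kept. The extra DVR pre-test is an assessment; the model's time factor has one Pre level.
- That the analysed number falls below 24 per arm already at 5% missing per visit. That requires counting a missing baseline against listwise exclusion (30 × 0.95⁵ = 23.2) but not against the comparator (28.5). Baseline is a covariate, so a patient without it would also be lost from the mixed model unless it were imputed. With baseline present, 24.4 remain.
- That missingness differs between EVR and DVR and follows recovery. The difference in visit burden makes this plausible, but the article does not document it.

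**Conclusion.** The point holds. As written, the main missing-data approach is listwise exclusion under MCAR, which sits badly with a five-visit random-intercept mixed model. Taken at patient level, it would remove patients who have the primary outcome and abandon validity under MAR; taken at record level, the MCAR statement is wrong.

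The loss of power is modest at low missingness (0.82 against 0.88 at 5% per visit) and material at higher rates (0.73 against 0.86 at 10%). These sizes rest on assumed rates, on independent misses in all but the dropout example, and on an assumed 80% power target. A fall below 24 per arm is conditional on more than about 5.4% missing per visit under the independent pattern; it is not a certainty. Selection bias between EVR and DVR is possible, and its size cannot be stated from the article.

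**What to change.** Replace the sentence with a short paragraph stating that:
- the primary analysis is the likelihood (REML) mixed model on all available ARAT visits of all randomised patients, in the arm assigned, under MAR;
- no patient is excluded for a missed visit;
- multiple imputation remains the sensitivity analysis, directed at departures from MAR;
- a complete-case analysis, if shown at all, is supplementary.

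The particular form of imputation can be left to the statistical analysis plan. The cost is one paragraph: the model is already planned and no new data are needed.

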### Current Results

Currently, there are seven subjects who have met the eligibility criteria, completed the training or usual care, and had their 6 month retention tests. The screening for patients is on-going. The estimated enrollment is 25–30 patients/year.

### Anticipated Results

Clinical outcome measures will be assessed in combination with the kinematic/kinetic and neurophysiological measures to determine whether; (1) early intensive training that focuses on the hand results in a more functional hemiparetic upper extremity, (2) there is an optimal early time period in which rehabilitation will be most effective, (3) it is necessary to initiate intensive arm and hand therapy during the early inpatient rehabilitation phase or will comparable outcomes be achieved if therapy is initiated right after discharge and, (4) there is a difference in the recapture of premorbid patterns of movement vs. the development of an efficient, but compensatory movement strategy.

## Discussion

This study focuses on arm and hand rehabilitation that (1) can be delivered in an inpatient rehabilitation facility during the early period of heightened neuroplasticity using VR/robotic simulations to facilitate the delivery of increased intensity of an intervention, (2) can quantify intensity to distinguish between total therapy time and actual movement time, (3) can specifically target the particular movement deficits that need to be modified, and (4) can incorporate patients with minimal movement. Independent upper extremity function is critically important to restore full independence and reduce the need for costly supportive care. One of the issues that may contribute to less than satisfactory outcomes for the hand (as well as the arm) is the complexity of hand motor control that involves coordination of multiple degrees of freedom. Early hand therapy is often limited when patients have not recovered sufficient motor function to utilize the hemiparetic hand during functional activities. Frequently therapists train compensatory movements using the less affected upper extremity, in an effort to attain maximal independence prior to patient's discharge in the face of the ever-decreasing length of stay in inpatient rehabilitation as part of a stroke care plan. This VR/robotic system is well-suited for the delivery of hand and arm training for more affected patients. Sensory and perceptual affordances provided by the integration of VR and robotics can target the unique hand deficits that one cannot address in real-world therapy (37), and thus possibly allow for functional improvement to move beyond the spontaneous recovery predicted in the literature (62).

The *NJIT/RAVR* and *NJIT-Track Gloves* systems have adaptive algorithms to drive individual finger movement, can modify the workspace to increase range of motion and can provide gain modification in order to allow a patient with a minimal amount of hand movement to interact successfully with the virtual reality simulations (37). Evaluating treatment response can be substantially improved with the addition of kinematic analyses (59). Currently used clinical assessments provide uncertain measures of a patient's progress and improvement due to a lack of sensitivity and potential ceiling effects. Multiple sources indicate that analysis of treatment response and understanding of recovery and compensatory processes can be substantially improved by incorporating analyses of kinematic/kinetic variables into clinical research studies (60). Measures that focus purely on task completion do not discriminate between neural recovery and functional compensation (16). Several authors suggest that kinematic analysis may provide a more effective way to measure the recovery of motor function following stroke (59, 61). More specifically, a lack of longitudinal analysis of 3D kinematics of functional upper extremity movements during early stroke recovery limits our true understanding of what motor changes actually occur and what patients actually learn during the early intervention period (61).

We hope that TMS and EEG will increase the ability of our study to generate translational, neurophysiologic data. We will quantify and relate neural reorganization of the corticospinal system and the cortical networks in both ipsilateral and contralateral hemispheres with behavioral (clinical and kinematic) recovery during the first 6 months post-stroke. While neurophysiological measures are considered promising biomarkers of corticospinal integrity and recovery, there are few studies utilizing these approaches to date (62, 63) and there has been no single well-controlled study examining changes in the trajectory of neural recovery subsequent to intensive, progressive therapy initiated at different stages, early post-stroke.

At the end of this project, we will characterize the effects of dosing and timing and determine whether (1) there is an optimal early time period in which rehabilitation will be most effective and when intensive training focused on the hand will result in a more functional hemiparetic arm, (2) it is necessary to initiate intensive hand therapy during the very early inpatient rehabilitation phase or will comparable outcomes be achieved if the therapy is initiated right after discharge, in the outpatient period when the cost of care is less, (3) early training results in a difference in the recapture of premorbid movement patterns vs. the development of an efficient, but compensatory movement strategy, and (4) whether patterns of cortical reorganization explain the prognosis for recovery. However, we will not be able to investigate the timing by dosing interaction and this is a limitation of the study.

The findings from Aim 1 will advance our understanding regarding the optimal time frame for the initiation of intensive rehabilitation. Knowledge gained in Aims 2 and 3 will provide a window into the mechanism of action underlying a rehabilitation intervention by advancing our understanding of the kinematic and neurophysiologic mechanisms underlying the recovery process mediated by this intensive and progression intervention. Importantly, we will have provided much-needed data for clinicians on the optimization of the timing of therapeutic interventions. This information will be relevant whether the rehabilitation is performed using more traditional means or whether it delivered through newer technology. Optimizing rehabilitation strategies and providing a means to deliver the intensity and progression of practice required for modifying neural architecture opens the window to potential new methods of rehabilitation. The idea that therapy can be used as a vehicle for driving neural reorganization is relatively new and will serve as a foundation for developing further novel therapeutic interventions based on neuroscientific principles.

It is evident that providing additional, intensive therapy during a stay in an inpatient rehabilitation facility is more complicated to implement, and difficult for patients to tolerate, than initiating it in the outpatient setting, immediately after discharge. To date, we have successfully integrated intensive hand therapy into an inpatient rehabilitation protocol. The next step in this line of inquiry will focus on developing an understanding of the interactions occurring between 3 critical elements: (1) a focus on the recovery of hand function, (2) facilitation of progressive and intensive training through the use of robotically facilitated, virtually simulated rehabilitation interventions, (3) beginning training early after stroke, during the period of heightened neuroplasticity. This study will fill a critical gap in the literature and make a significant advancement in the investigation of putative interventions for recovery of hand function in persons with stroke.

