### Study Aims and Hypotheses

This study is designed to empirically test the controversy regarding both the value of intensive, high dosage training as well as the optimal timing for intensive VR/Robotic training in the first 2 months after stroke. We are continuing an ongoing investigation into the effects of intensive task and impairment-based training of the hemiparetic upper limb with a focus on the hand using robotically facilitated rehabilitation interventions presented in virtual environments. The primary aim of this study is to test, at 4 months post-stroke, whether adding intensive VR/Robotic motor training to a patient's standard of care rehabilitation at 5–30 days post-stroke, improves functional outcomes of the hemiparetic hand when compared to initiating the additional VR/Robotic motor training 30–60 days post-stroke; thus testing the concept of optimal timing. Other comparisons include comparing Early VR to dose-matched usual care to test the potential benefits of the high-intensity VR/Robotic intervention. Comparing dose-matched usual care (10 additional hours of standard therapy) to usual care (no additional therapy) will inform about the benefits of increased dosing (Table 1). See controversies elucidated in recent literature (12, 30). We hypothesize that the outcomes will favor the early, high dosage VR/Robotic hand training group when compared to the delayed VR/Robotic training group and dose matched usual care group. The secondary aims will systematically investigate the mechanisms underlying the changes resulting from early timing of training and increased dosing, specifically changes in kinematics, kinetics, patterns of cortical somatotopic reorganization, and brain connectivity. We further hypothesize that the early, high dosage VR/Robotic hand training group will show a larger relative contribution of restored kinematic motor patterns to the overall improvement in motor function and these functional gains will be associated with the expansion of ipsilesional hand cortical somatotopy.

**Table 1 T1:** Comparison groups.

**Group comparisons**	**Intervention period^**+**^**	**Test**
EVR vs. DVR^*^	5–30 vs. 30–60 days	Timing of a VR/robotic intervention
EVR vs. DMUC^**^	5–30 days	VR/Robotic vs. conventional intervention
DMUC vs. UC^***^	5–30 days	Dosing of an intervention

* Early Virtual Reality vs. Delayed Virtual Reality,

** Dose Matched Usual Care,

*** *Usual Care; ^+^Time Post-Stroke*.

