### Statistical Analysis

The primary aim of the study is to test, at 4 months post-stroke, whether intensive VR/Robotic motor training initiated 5–30 days post-stroke, improves functional outcomes of the hemiparetic arm and hand when compared to VR/Robotic motor training initiated on 30–60 days post-stroke. Other comparsions include evaluating the type of training (EVR vs. DMUC) and dosing (DMUC vs. UC) initiated within 5–30 days post-stroke. The secondary aims will systematically investigate the mechanisms underlying the changes resulting from the early timing of training and increased dosing. Aim 2 will quantify the recovery and compensation profiles by examining the changes in kinematics and kinetics of the hand and arm associated with this training and Aim 3 will quantify patterns of cortical somatotopic reorganization and will investigate the relationship among these patterns of reorganization and the clinical and biomechanical outcomes.

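### The protocol says it will determine whether a post-discharge start gives comparable outcomes, but the EVR–DVR comparison is planned and sized only to detect a difference

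*Protocol article*

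**What the plan says.** Two places in the protocol article describe what the EVR–DVR comparison will settle. Anticipated Results asks whether intensive therapy must begin during the inpatient phase or "will comparable outcomes be achieved if therapy is initiated right after discharge". The Discussion repeats this among the matters the project will determine by its end, and adds cost: "will comparable outcomes be achieved if the therapy is initiated right after discharge, in the outpatient period when the cost of care is less".

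The operational sections ask a different question:

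- **Study Aims and Hypotheses:** "We hypothesize that the outcomes will favor the early, high dosage VR/Robotic hand training group when compared to the delayed VR/Robotic training group".
- **Statistical Analysis, primary aim:** whether early training "improves functional outcomes of the hemiparetic arm and hand when compared to VR/Robotic motor training initiated on 30–60 days post-stroke".
- **Statistical Analysis, contrasts:** "the timing comparison is the difference between EVR and DVR". It is tested as a group-by-time interaction with a Tukey or Bonferroni adjustment.
- **Sample Size:** 24 per group are "required to detect the effect size of 0.42 between EVR and DVR or between UC and DMUC over time", "for significance level 0.05". The total is raised to 120 for attrition, and an interim analysis with a sample size update is planned at 50% recruitment.

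The article gives no margin within which the two start times would count as comparable.

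**The concern.** The two statements are framed as either/or: an early start is necessary, or outcomes are comparable. They leave no place for an inconclusive result. A test for a difference has two outcomes, difference shown or not shown, and the second does not establish comparability. If the EVR–DVR contrast is non-significant, the wording invites the conclusion that patients can wait for the cheaper outpatient period. At this sample size, such a result would be quite likely even if early training had a real advantage well worth knowing about.

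**Working it through.** **Inputs from the Sample Size section.** f = 0.42; alpha 0.05; 24 per group for the contrast; 120 in total, so 30 per group. Power is not stated. The SD of ARAT change is not stated either, so results are in SD units of the analysed change.

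**Step 1. Reproduce the plan's figures.** Use a noncentral F test with noncentrality λ = f²N.

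- EVR–DVR contrast, N = 48, df (1, 46): λ = 0.42² × 48 = 8.47, power 0.813. At N = 46 power is 0.796, so 48 (24 per group) is the smallest even N reaching 80%.
- Overall 4 × 3 interaction, N = 84, df (6, 160): λ = 0.42² × 84 = 14.82, power 0.821. At N = 80 power is 0.797. This matches the statement that "a total of 84 patients (21 for each group) are needed to detect the overall Treatment Group" interaction.
- Attrition: 96 / (1 − 0.20) = 120.

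Both stated sizes are those of a test for a difference at unadjusted alpha 0.05 with an inferred 80% power. For two equal groups d = 2f = 0.84 SD.

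**Step 2. Precision of the EVR–DVR difference.** Half-width = t(0.975, 2n − 2) × √(2/n).

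- n = 24: 2.013 × 0.2887 = 0.58 SD.
- n = 30: 2.002 × 0.2582 = 0.52 SD.
- Bonferroni for the three contrasts of a priori interest (alpha 0.05/3): 0.72 SD at 24 and 0.64 SD at 30.

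With an observed difference of exactly zero, the interval at 24 per group still reaches 0.58 SD either way. With an estimate just short of significance it runs from about 0 to 2 × 0.58 = 1.16 SD, which includes the whole 0.84 SD design effect.

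**Step 3. Chance of a non-significant result when early training is truly better.** Noncentral t, two-sided.

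| True advantage | 24 per group | 30 per group | 24, Bonferroni | 30, Bonferroni |
|---|---|---|---|---|
| 0.42 SD (half the design effect) | 70% | 64% | 84% | 79% |
| 0.60 SD | 47% | 37% | 65% | 55% |
| 0.84 SD (design effect) | 19% | 11% | 34% | 22% |

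**Step 4. What a comparability claim would need.** The documents give no margin, so a range is shown: non-inferiority, one-sided 0.025, true difference 0, normal approximation, n per group = 2(1.960 + 0.842)² / margin².

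| Margin | n per group for 80% power | Power at 24 / 30 per group |
|---|---|---|
| 0.84 SD | 23 | 83% / 90% |
| 0.60 SD | 44 | 55% / 64% |
| 0.50 SD | 63 | 41% / 49% |
| 0.42 SD | 89 | 31% / 37% |

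Only a margin near the full design effect fits the planned size. For a two-sided claim, a 95% CI with half-width 0.52 to 0.58 SD cannot fit inside a margin of that size or smaller, whatever the estimate.

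**Illustration in ARAT points.** Assuming the SD of 4-month change lies between 8 and 15 points, the half-width at 24 per group is 0.581 × 8 = 4.6 to 0.581 × 15 = 8.7 points on the 57-point scale. At 30 per group it is 4.1 to 7.8 points.

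**The case against.** The strongest reply is that these are forward-looking sentences in Anticipated Results and the Discussion. The stated aim, hypothesis, contrast and sample size form a coherent superiority design, and no endpoint or decision rule depends on the word comparable. That stands, and it limits the point to what the trial says it can conclude. A reader might infer that comparability is a formal objective, or that the primary test is flawed. The documents support neither.

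A reader might also infer that the investigators intend to report a null result as comparability. Nowhere do they say so. The mixed-model contrasts yield an estimate from which an interval can be reported, so failure to reject is not the only available route. What can be said is that the either/or wording permits the misreading. The limitation the Discussion does name, the timing-by-dosing interaction, is a different one.

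The absence of a confidence-interval rule is not itself a fault in a condensed article, since a separate analysis plan may hold one. The finding rests on what the article states: a conclusion that its own sample size supports only at a very wide margin.

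The calculation is simplified. The planned baseline covariate could help: under the stated correlation of 0.7 and compound symmetry, residual variance relative to the change score is (1 − 0.7²) / (2(1 − 0.7)) = 0.51 / 0.60 = 0.85. Half-widths then shrink by √0.85 = 0.92, to about 0.54 and 0.48 SD. The multiplicity adjustment works the other way, and the interim update could change the size. None of these turns a null result into evidence of comparability.

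**Conclusion.** The point holds as a mismatch between a stated conclusion and the design. The article says the trial will determine whether delayed training gives comparable outcomes, while the EVR–DVR comparison is a difference test sized for 0.84 SD of change. A non-significant result would leave open differences of at least 0.52 to 0.58 SD, and would occur about 64% to 70% of the time if early training were truly better by 0.42 SD.

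These figures assume 24 to 30 completers per group, a two-sided test at 0.05 without multiplicity correction, and a two-sample comparison of change. The 80% power is inferred, and the ARAT-point values are illustrative only. The superiority test itself, its error rate and its sample size are not in question here.

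**What to change.** 1. In Anticipated Results and the Discussion, replace the necessary-or-comparable wording. Say that the trial tests whether an early start is superior to a delayed start and estimates the EVR–DVR difference in 4-month ARAT with its 95% CI.
2. In Statistical Analysis, next to the EVR–DVR contrast, state how a non-significant result will be reported: no difference shown, and differences up to the CI limits not excluded. It will not be reported as comparability, or as evidence that an early start is unnecessary.
3. Keep a comparability claim only if a justified margin is fixed before the interim analysis at 50% recruitment. Acknowledge that the planned size supports only a margin near 0.84 SD; a narrower one would mean resizing, for example about 89 per group at 0.42 SD.

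Items 1 and 2 are changes of wording and touch no trial procedure. Their price is that the trial gives up the comparability and cost message after a null result. Item 3 is not free unless a very wide margin can be defended.
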